
Another important goal in the recent panorama is the issue of personalization. The possibility to customize interventions based on the specific patients’ need is the aim of the growing scenery in medicine. An increasing number of studies recommend a personalized approach instead of a standard procedure that considers patients in their homogeneity whereas each one is unique despite its pathology [28,29]. To respond to the demand of cutting-edge requirements, we propose a novel approach to forecast which motor or cognitive indicators are most revelatory of long-term maintenance of any improvements obtained. The aim is to verify whether the proposed treatment can be effective in the population according to their clinical characteristics. Estimating the treatment effect, the so-called Treatment Effect Prediction (TEP), is crucial in disease management because it ensures that patients receive the expected clinical outcomes [30]. Machine Learning (ML) techniques offer a great opportunity; they may allow the selection of the most predictive variables, which will be empirically verified via follow-up, also improved based on the historical data of patients, results of neuropsychological traditional tests, and the information provided by the VR system. Using DT tasks, clinicians dispose of a great amount of data compared to a single one, concerning different cognitive indexes and motor variables; additionally, using VR System, allows combining complex tasks providing an even greater amount of data. Thus, a linear approach could be not sufficient, and it may be necessary a multivariate approach, such as ML. ML may be more informative thanks to data fusion, integrating data in a nonlinear model which proves information about treatment prediction. Data from the cognitive, motor, and DT assessment initial evaluation can be compared to ML clinical data and the great amount of features detected during the combined VR intervention to see whether and how patients’ baseline state influenced and predicted rehabilitation outcomes.

The main aim of the present protocol is to create and validate a VR-based program for patients with motor and cognitive impairment. To assess cognition and physical aspects we propose a specific neuropsychological battery, described below. The secondary aim is to improve the quality of life in a sample of older adults with Parkinsonian Syndromes [31], preventing negative outcomes.

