## Experimental design

The protocol aims to improve motor and cognitive deficits in patients with Parkinsonian Syndromes. A clinical examination will verify the inclusion and exclusion criteria. The eligible subjects will be assessed, and outcome measures will be collected (t0) by a trained physiotherapist and psychologist. The specialist who assesses participants will not train them. Patients will be then randomly assigned to a control or experimental group using a randomization sequence obtained from the website randomizer.org. The first group will complete the treatment as usual (TAU). Usually, training consists of a series of neuropsychological exercises delivered in paper and pencil modality, and classic motor activity, comprehending aerobic and anaerobic activities delivered thanks to bodyweight exercises on a stationary bike in an ordinary gym. The other one will complete a VR dual-task training protocol. Based on the evidence that exercise programs with shorter session duration and higher frequency may generate the best results [23], we propose 4–5 weeks of training of 10 sessions of 1 hour approximately, two times a week. Completed the 10 biweekly rehabilitation sessions a new assessment will be done (t1). The neuropsychological and motor assessment will be carried out before (t0), immediately after (t1) and 3 months after the end of the 10 sessions (t2) to evaluate the short/medium-term efficacy of the treatment. The chart of the trial design is presented in Fig 1. Patients must attend at least 8 out of 10 rehabilitation sessions as well as all the assessments for the treatment to be considered effective. All participants will sign the written informed consent.

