Test	Outcomes information
*Motor*	
Tinnetti Balance Scale	Balance
Equiscale	Standing and resistance to external and self-induced perception
TUG	Mobility
*Cognitive*	
MMSE	General cognitive status
FAB	Screening of executive function
ToL	Reasoning and problem-solving
TMT	Attention and set-shifting
Stroop Test	Cognitive flexibility and sensitivity to interference
*Dual-task ability*	
Motor and cognitive TUG	Balance and executive functions
WART	Gait and working memory
**Questionnaire**	**Outcomes information**
PDQ-39	Quality of life

Moreover, we will consider outcome variables provided by the CAVE system during the DT training such as the time, accuracy, velocity, etc. performing each exercise.

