## Data analysis

We will realize a mixed design trial (2x3) with population training (VR vs. TAU) as a between variable and assessment of training effect (pre-test, post-test, and follow-up) within variables. A Windows Excel sheet will be used to organize all the data related to demographic and assessment information and an identification code will be assigned to each participant to ensure anonymity of the data. A mixed ANOVA will be performed to investigate interaction effects between and within variables.

Moreover, we will analyze the accuracy during DT training to verify possible correlations with the accuracy measure in the assessment part at t0 and t1. The objective will be to examine if traditional tests reflect trained abilities.

Moreover, we will propose an innovative approach of ML in the rehabilitation field, to estimate the TEP from the collected data during the DT VR experience. Based on our research question and available data we will use a classification algorithm to create a model; we will train and test the model using data to forecast which motor or cognitive parameters are more predictive for the future maintenance of any improvements obtained, based on the model proposed by Shi and colleagues (2019) [44]. We will use one of the best programs for ML analysis, such as Python.

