The use of DT and new technology joined with collecting big data useful to integrate with outcomes provided from the assessment offering more reliable and predictive neuropsychological results compared to the classic paper and pencil tests. The application of ML techniques could optimize individual treatment strategies, helping the transition to personalized, effective, and engaging medicine, built on the individual patient’s needs. In the literature, ML is linked to diagnostic screening methods, with subsequent disease progression analyses [50–52]. Using ML in the rehabilitation field is a new strategy that allows exact predictions on which motor or cognitive measures are more predictive of future maintenance of any improvements obtained. Identifying such aspects could promote the movement away from a one-treatment-suits-all-approach to the development of personalized treatment in the context of the broad spectrum of cognitive training interventions. In this scenario, clinicians could know which patients’ characteristics predict the efficacy of different training modes and what type of training works best. Health professionals could also save patients’ time in the assessment phase by providing training quickly and efficiently. Indeed, interventions that are specific and well-timed are required to maintain cognitive performance and decrease the progression of dementia and physical decline. For example, early detection of gait abnormalities allows for the timely identification of not just motor risk but also cognitive loss, allowing for appropriate intervention [53]. Further, in some cases, it could be more effective to use vertical therapy than a traditional dual-task or a VR dual-task, providing long-term improvement in rehabilitative outcomes. Therefore, ML can augment the ability of healthcare providers to improve patient care, deliver accurate diagnoses, optimize treatment plans, inform decisions, or allocate resources within health systems [56,57].

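### The Treatment Effect Prediction is to be estimated from VR-session data, which exist in one arm only; as written it is a prognostic model, not a treatment-effect model

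*Protocol article*

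**What the plan says.** Four parts of the protocol article bear on this.

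- **What TEP means (Introduction).** "Estimating the treatment effect, the so-called Treatment Effect Prediction (TEP), is crucial in disease management". The stated purpose is to "verify whether the proposed treatment can be effective in the population according to their clinical characteristics".
- **What TEP is estimated from (Data analysis).** The plan is "to estimate the TEP from the collected data during the DT VR experience". A classification algorithm is named, and "we will train and test the model using data to forecast which motor or cognitive parameters are more predictive" of later maintenance of whatever improvement was obtained.
- **Where those data come from (Outcome measure, Experimental design).** The session measures are "outcome variables provided by the CAVE system during the DT training such as the time, accuracy, velocity, etc". The control arm receives "neuropsychological exercises delivered in paper and pencil modality, and classic motor activity" in an ordinary gym and does not use the CAVE.
- **What the result is for (Discussion).** Clinicians could learn which patients' "characteristics predict the efficacy of different training modes and what type of training works best". The Discussion also describes machine-learning predictions in rehabilitation as exact.

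**The concern.** A treatment effect is a contrast between what happens under VR and what happens under TAU. Effectiveness by patient characteristics is a statement about how that contrast varies, which is effect modification. The data source named for TEP covers one side of the contrast only. A classifier of maintained improvement built on it ranks patients by how well they do after VR training. A patient who would have kept the same gains under TAU looks exactly like one who kept them because of VR.

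The session measures are also recorded after randomisation and have no TAU counterpart. They cannot enter an arm comparison as baseline modifiers, and they are not available when someone must choose a training mode before it starts.

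At stake is the personalisation aim, which the Abstract, Introduction, Data analysis and Discussion all put forward. If a prognostic model is reported under the name TEP, readers may use it to choose between VR and usual care, which it does not inform.

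**Working it through.** **1. Size of the VR arm.** The Participants section gives a final sample of 45, from an effect size of 0.43 (metric not named), alpha 0.05 and 80% power. Read as Cohen's f for two groups, the noncentrality is f² × N = 0.43² × 45 = 8.32 on 1 and 43 degrees of freedom, and power is 0.805. With N = 44 it is 0.796, so 45 reproduces. (A two-sided paired t-test with a standardised difference of 0.43 also gives 45.) The allocation ratio is not stated. Under an assumed 1:1, 45/2 gives 22 or 23 VR patients.

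**2. Which inputs exist in which arm.**

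| Input named in the article | VR | TAU | Timing |
|---|---|---|---|
| CAVE time, accuracy, velocity | yes | no | after randomisation |
| Motor, cognitive and dual-task tests at t0 | yes | yes | before randomisation |
| Patient history | yes | could be supplied | before randomisation |

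The TEP sentence in Data analysis points to the first row.

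**3. Can VR-arm data identify the effect?** Take one feature x, standard normal, with probability of maintenance under VR = 1/(1 + exp(−x)). The AUC for maintenance in the VR arm is then 0.74. Consider two possibilities for TAU:

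| | VR minus TAU, x > 0 | VR minus TAU, x ≤ 0 |
|---|---|---|
| A: TAU follows the same curve | 0 | 0 |
| B: TAU maintenance is a flat 50% | +17 points | −17 points |

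The VR-arm data are identical in A and B. No algorithm, tuning or larger VR arm can separate them. Overall maintenance is also 50% in both arms under both scenarios, so a comparison of overall rates would not separate them either. Only a model with both arms and an arm-by-x term can. If x is a CAVE measure, it is not observed under TAU and that model cannot be fitted.

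**4. What both arms would give.**

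- *AUC.* Hanley–McNeil at AUC = 0.75: Q₁ = 0.75/1.25 = 0.600 and Q₂ = 2 × 0.75²/1.75 = 0.643. With 11 against 11 patients, variance = [0.1875 + 10(0.600 − 0.5625) + 10(0.643 − 0.5625)]/121 = 0.0113. The SE is 0.106 and the 95% half-width 0.21. With 23 against 22 the half-width is 0.14.
- *Accuracy.* Clopper–Pearson for 16/22 is 50% to 89%; for 34/45 it is 60.5% to 87.1%.
- *Interaction.* Assume 1:1 allocation and an evenly split binary predictor. The four cells hold 45/4 = 11.25 patients each. The SE of the difference of differences is σ√(4/11.25) = 0.60σ, a 95% half-width of 1.96 × 0.60σ ≈ 1.2σ, where σ is the residual SD of the t2 score.

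**5. A caution on optimism.** With 22 patients split 11/11 and pure-noise features, the best single-feature apparent AUC averages 0.77 with 20 features and 0.79 with 30. With 45 patients it is 0.69 and 0.70. The feature count is an assumption: over 12 to 100 features the 22-patient figure runs from 0.75 to 0.83.

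**The case against.** The strongest reply is that the article does not confine machine learning to CAVE data. The Introduction also lists patients' history and traditional test results, and says the initial assessment will be used to see how baseline state predicted outcome. Those inputs can exist in both arms, and no sentence excludes TAU patients. This stands. A reader might infer that the trial cannot support any treatment-effect model; the documents do not support that. What remains is that the analysis text ties TEP to the VR experience and describes no two-arm model.

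Second, the operational target, maintenance of improvement, is itself prognostic, and a within-VR classifier can address it. That is true, and it narrows the problem to the mismatch between this target and data source and the name and aim attached to them. The model follows a cited method that is not available here, so how that source uses a comparator is unknown.

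Third, the Discussion sentences are conditional or general, and the aim in the Introduction does not itself mention TAU. This is fair: they are claims to be kept within bounds, not specified estimands. But knowing which training works best does require a comparison of trainings.

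A reader might also infer from the small sample that features will be selected outside cross-validation, or that one small test set will be held out. The article says neither. Its wording on training and testing is compatible with cross-validation, and such detail may sit in the full plan. The noise figures are therefore only a caution, not evidence of a planned error.

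**Conclusion.** The point holds as an inconsistency in what the article states. TEP is defined as estimating the treatment effect, yet it is to be estimated from data that only the VR arm can produce, without any described arm term or interaction. The result would be prognosis after VR training. It would not show benefit from VR over TAU, and a VR-arm AUC of 0.74 is compatible with no effect modification or with a swing from +17 to −17 points.

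The identifiability argument does not depend on sample size. The figure of 22 or 23 patients assumes 1:1 allocation and no losses. The ±17 points come from an illustrative model, not from trial data.

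The mixed ANOVA comparison of VR with TAU is unaffected. This should be corrected because personalisation is a prominent aim, but it does not threaten the randomised comparison.

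**What to change.** 1. **Relabel.** Call the model using VR-session features an exploratory prognostic analysis within the VR arm, and do not call it TEP.
2. **Use both arms for any treatment-effect or personalisation claim.** Model the t2 score on the t0 score, arm, a short pre-named list of t0 predictors, and the arm-by-predictor terms. Penalise the interactions, validate internally with every modelling step repeated in each resample, and label the analysis exploratory.
3. **Limit the claims.** Restrict the Discussion statements on exactness of prediction and on which training works best to what analyses 1 and 2 can show.

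No new data, visits or patients are needed, because the t0 and t2 assessments are already planned. The cost is some rewording, modest analysis time and a smaller machine-learning claim. With 45 patients the interactions stay imprecise (half-width about 1.2 residual SD in the simplest case above), so analysis 2 can suggest modifiers for later study but not settle them.

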## Discussion

This VR dual-task rehabilitation protocol aims to assess and train motor abilities and executive function in older people characterized by a deterioration in either motor or cognitive execution or even both, capitalizing on the massive amount of information extrapolated from patients during their diagnosis and treatment process, thanks to ML. The final scope is also to improve patients’ quality of life, considering that most daily activities require dual-task abilities. Considering these premises, we evaluate the ability to perform DT by using exercises as similar as possible to what people encounter in daily life. We will develop an innovative tool employing an immersive VR system and we will compare this innovative protocol with a selection of traditional exercises. Based on promising literature on VR and DT training, the presented protocol could be as effective as or more effective than classical rehabilitation. Several studies showed that combining physical and cognitive training is more successful compared to a single physical or cognitive exercise [27]. Moreover, the use of VR seems to be a crucial element to enhance successful and fulfilling rehabilitation [26,45]. VR has an important value in rehabilitation: it provides an intervention program based on the latest technological advances that act on crucial components of daily life. Based on the literature, the presented protocol seems to be promising in training motor and cognition. However, further studies will analyze the usability and the clinical efficacy of the tool, also examining participants’ perceptions of the used technology.

Moreover, recent researchers underline the importance of proposing continuative assistance to contribute to the maintenance of obtained benefits. New challenges and opportunities come from Ambient Assisted Living which can help people at home in many ways, including social integration, health, lowering the risk of cognitive decline, and preventing premature death. This innovation could improve the wellness and health conditions of older adults, allowing the prevention and management of diseases. Nowadays, AAL includes tools such as medication and events reminders [46], monitoring systems for fall detection [47,48], assistive devices in the activities of daily life [49,50], and technologies to promote a healthier lifestyle and socially-active aging [51]. New ideas of application proposed to train motor and cognitive abilities are arising [48,52]. Accordingly, this new protocol might be customized to be used at home, providing a tablet-based tool with a portable cycle ergometer to perform the dual-task exercise. Although this modality could not as immersive as the one provided with the CAVE, it could be an effective solution to promote the continuity of care also in patients that access in hospital for a limited period, providing a presumably safer environment to train them for the dual-task challenges with practical applications [53–55], which reflect ecological situations. In these panoramas, it could be useful to promote joined interventions which include both in-hospital interventions followed by at-home training to retain the improved capabilities.

The use of DT and new technology joined with collecting big data useful to integrate with outcomes provided from the assessment offering more reliable and predictive neuropsychological results compared to the classic paper and pencil tests. The application of ML techniques could optimize individual treatment strategies, helping the transition to personalized, effective, and engaging medicine, built on the individual patient’s needs. In the literature, ML is linked to diagnostic screening methods, with subsequent disease progression analyses [50–52]. Using ML in the rehabilitation field is a new strategy that allows exact predictions on which motor or cognitive measures are more predictive of future maintenance of any improvements obtained. Identifying such aspects could promote the movement away from a one-treatment-suits-all-approach to the development of personalized treatment in the context of the broad spectrum of cognitive training interventions. In this scenario, clinicians could know which patients’ characteristics predict the efficacy of different training modes and what type of training works best. Health professionals could also save patients’ time in the assessment phase by providing training quickly and efficiently. Indeed, interventions that are specific and well-timed are required to maintain cognitive performance and decrease the progression of dementia and physical decline. For example, early detection of gait abnormalities allows for the timely identification of not just motor risk but also cognitive loss, allowing for appropriate intervention [53]. Further, in some cases, it could be more effective to use vertical therapy than a traditional dual-task or a VR dual-task, providing long-term improvement in rehabilitative outcomes. Therefore, ML can augment the ability of healthcare providers to improve patient care, deliver accurate diagnoses, optimize treatment plans, inform decisions, or allocate resources within health systems [56,57].

## Limitation and conclusion

Limitations apply to the current work as well. CAVE systems are not as common in healthcare settings because they are expensive technology solutions and need some space. There are currently commercial solutions available at low cost, such as the Head Mounted Display (HMD), much more portable and with a greater capacity for immersion and presence. However, the CAVE among the different types of VR is a tool that makes it possible to achieve a good level of immersion allowing motor exercises without limitations. This possibility is not as easy with other VR tools, such as HMD, which could limit the users’ movements. Users wear their HMD and they do have not a complete visual of anything that happens outside the visor; this could generate feelings of apprehension and they may reduce their movements. Moreover, the CAVE offers the possibility to recreate a more realistic dual-task situation: users may view their real bicycle while cycling in a park for example, improving their engagement and immersion in the task.

Another limitation concerns the possible negative effects of using VR, i.e., cybersickness. Cybersickness is a potential result of the intensive visual and motion cuing when encountering a virtual environment, and it is defined as a set of symptoms including nausea, weariness, headache, strain, postural instability, and vomiting [58]. However, we take into account some parameters which could minimize these consequences, such as considering realistic movements to match sensory expectations, creating a clear, steady horizon environment with reference points, and limiting the time of exposure [58].

Despite some limitations, the project arises from an emerging question in the research field and aims to contribute by providing several benefits also on services and the community. On one hand, the protocol aims to ameliorate autonomy and quality of life in a sample at risk of frequent falls and cognitive impairment; on the other hand, the project might improve the Italian healthcare system by providing innovative treatment based on recent advances in neuroscientific and technological research, opening new opportunities in this field.
